### 4.1 Population Definitions

Four patient populations will provide the basis for all statistical analyses and data presentations.

**Per Protocol (PP) population:** This will consist of all patients who receive at least 10 doses of randomised treatment within the first 7 days of the first dose of study medication. However, there were nine patients (014, 015, 016, 017, 020, 021, 032, 033, 034) who were either known to have had (n=2), potentially had (n=3), or were associated with patients who had (n=4), a discrepancy in dispensing of randomised therapy, these patients will be excluded from the PP population.

**Intent-To-Treat (ITT) population:** All randomised patients who receive at least one dose of study medication. This population will include the nine patients excluded from the PP population due to possible errors in dispensing.

The primary population for efficacy endpoints will be the PP population with select efficacy endpoints also analysed in the ITT population (see Section 6.2)

**Safety population:** All randomised patients who have taken at least one dose of study medication including the nine patients excluded from the PP population due to possible errors in dispensing. This population will be applied to all safety endpoints and pharmacokinetic data recorded in all patients. The safety population will be identical to the ITT population if all patients dosed have efficacy data recorded.

**PK Sub-Study population:** A group of up to 12 patients fitted with an EVD as part of their normal treatment are to be selected for the pharmacokinetic sub-study.

Given the early stage of development, the PP population is of primary interest and all patients will be analysed according to the treatment they actually receive in all populations. For the ITT population, if due to dispensing errors it is known patients received a mixture of SFX-01 and placebo capsules, they will be assigned to the arm for which they received medication for the majority of time.

In addition, clinically important protocol violations will be identified in a blinded manner and then summarised and listed in the clinical study report (CSR).

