### 3 Study Design

The study is a randomised, double-blind, parallel-group design comparing SFX-01 (300 mg bd) administered for up to 28 days versus Placebo control in 90 patients who meet the per-protocol criteria for efficacy analyses, who have had a SAH and are referred to neurosurgical units for tertiary care.

Treatment is taken twice-daily either orally or via nasogastric tube (NG). For the first 20 patients, treatment duration is determined by the length of time spent in tertiary care (up to Day 28 post ictus). Following a DSMB review (as per protocol) for all subsequent patients the intended treatment duration is 28 days regardless of whether they remain in tertiary care for the full 28-day period. After treatment all patients are then followed up at discharge from the neurosurgical unit and then subsequently on Day 28, Day 90 and Day 180 post ictus.

A separate and more detailed investigation (sub-study) of the pharmacokinetic properties of SFN parent drug, and the primary metabolite, both in CSF and blood is also undertaken. This will involve up to 12 patients who have an External Ventricular Drain (EVD) fitted as part of their normal standard of care and is undertaken on two separate occasions within the first 7 days post ictus.

The protocol was amended part way through recruitment to stratify the randomisation by WFNS score (1-3 v 4-5) and centre.

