#### 3.1 Sample Size

Following protocol amendment 5, the sample size was increased from 90 to up to 120 patients in order to provide 90 who would meet the per protocol criteria and be evaluable for the primary efficacy analysis. Furthermore, this protocol amendment also specified that patients who had potentially received insufficient or incorrect study medication may be replaced.

If the standard deviation is approximately half (53%) of the mean difference in the maximum MCA flow velocity, 90 evaluable patients will have 80% power to detect a statistically significant difference between treatment arms using a 1-sided type 1 error rate of 5%. Statistical significance will be declared if the 2-sided p-value is  $<0.05$ , in this case the trial will have  $>80\%$  power with 90 evaluable patients if the standard deviation is  $<59\%$  of the mean difference.

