## 5.2 Modified Rankin Score

The Modified Rankin Scale (mRS) is recorded at Day 7, 28, 90 and 180 as well as at discharge. mRS will be analysed as a score ranging from 0-6 as displayed in Table 2. Any patient who has died before the respective timepoint will be given a score of 6. Any mRS recorded at the discharge visit that is contained within the protocolled defined time-windows and is closer to the nominal time than any other recordings will be used at that timepoint.

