## 5.3 Glasgow Outcome Score Extended

The Glasgow Outcome Scale – Extended (GOSE) is recorded at Day 28, 90 and 180. GOSE will be analysed as a score ranging from 1-8 as displayed in Table 3. Any patient who has died before the respective timepoint will be given a score of 1.

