## **6.9 Changes from Protocol**

## EVG001SAH Statistical Analysis Plan

1. The use of modelling rather than hypothesis testing where possible to allow more powerful analysis through inclusion of covariates and the generation of treatment estimates with confidence intervals.
2. Refinement of the per-protocol definition to consist of patients who receive at least 10 doses of randomised treatment within the first 7 days post-ictus and to exclude patients with potential dispensing errors.
3. Clarification that mRS and GOSE at 90 days are key secondary endpoints

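### The 10-dose per-protocol rule drops early deaths and early stoppers from the primary efficacy set, and most clinical outcomes have no guaranteed all-dosed analysis

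*SAP*

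**What the plan says.** Section 4.1 of the SAP builds the PP set on exposure: "This will consist of all patients who receive at least 10 doses of randomised treatment within the first 7 days of the first dose of" [trial drug]. Nine named patients linked to dispensing discrepancies are also removed. The section then states: "The primary population for efficacy endpoints will be the PP population with select efficacy endpoints also analysed in the ITT population". The ITT set is wider: "All randomised patients who receive at least one dose of study medication". All sets are analysed by treatment actually received.

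The endpoint sections treat death as the worst outcome. For mRS (Section 5.2): "Any patient who has died before the respective timepoint will be given a score of 6". For GOSE (Section 5.3): "Any patient who has died before the respective timepoint will be given a score of 1". A patient who has died gets 0 on every SF-36 item (5.7), 3 on CLCE-24 (5.8), 5 on BICRO-39 (5.9) and category 9 on SAHOT (5.10). For length of stay (5.11), a death before discharge is censored one day beyond the longest observed stay. DCI, new infarct and Triple H have no death rule.

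Section 6.2 plans TCD, mRS and GOSE in both PP and ITT, with PP primary. The remaining endpoints are run in PP and move to ITT only if results in the two sets disagree meaningfully, a condition that is not defined. Section 7 (General Information) limits summaries of those other secondary efficacy endpoints to PP. Section 6.3 names mRS and GOSE at 90 days as the key secondary endpoints.

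Section 3.1 records that "the sample size was increased from 90 to up to 120 patients in order to provide 90 who would meet the per protocol criteria", and allows replacement of patients with insufficient or incorrect medication.

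**The concern.** Membership of the primary set depends on something that happens after randomisation and is linked to prognosis: surviving and staying on treatment long enough to take ten doses. The endpoint definitions count death as the worst result, while the population definition removes the earliest deaths before they can be counted. The two rules work against each other.

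If treatment affects early death or early stopping, the PP arms are no longer comparable by randomisation, and the PP result describes patients who got through the first days. Two secondary objectives in Section 2 ask whether up to 28 days of treatment reduces DCI or improves long-term outcome, with no minimum exposure. The PP set does not answer those without a further assumption about early loss. The gap is widest for the eight endpoints that may never be analysed in all dosed patients.

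**Working it through.** **Time of the tenth dose.** Dosing is twice daily (Section 3). At 12-hour spacing, dose 10 comes 9 × 12 h = 108 h = 4.5 days after dose 1. Ten doses are 10/14 = 71% of those scheduled in 7 days. Nobody who dies or permanently stops before that point can be in PP.

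**The plan's own figure.** 90/120 = 75%, so up to 30 patients (25%) may fall outside PP. Nine are the named dispensing cases, leaving up to 21 for any other reason. This is a ceiling; the SAP does not say how many would be early deaths.

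**A second clock.** Section 6.9 describes the same rule as "at least 10 doses of randomised treatment within the first 7 days post-ictus". Taking 7 days as 168 h, a first dose at 48 h leaves 120 h, or ten scheduled doses before the limit, so one missed dose would exclude the patient. The two wordings need reconciling. The point here holds under either.

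**Effect on an odds ratio.** The SAP gives no early-death rate and no mRS distribution, so both are assumed.
- Placebo mRS 0 to 6 among patients reaching ten doses: 12/22/20/16/12/8/10%.
- SFX-01 in PP: the same distribution, shifted by the PP odds ratio for a better score.
- All-dosed distribution in each arm, with early-death fraction e: every PP proportion × (1 − e), with e added to score 6.
- A proportional-odds model is fitted to the expected proportions, with equal arms.

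| Early deaths, SFX-01 / placebo | OR in PP | OR in all dosed |
|---|---|---|
| 5% / 5% | 1.00 | 1.00 |
| 8% / 2% | 1.00 | 0.85 |
| 15% / 5% | 1.00 | 0.76 |
| 2% / 8% | 1.00 | 1.18 |
| 6% / 6% | 1.67 | 1.58 |
| 6% / 3% | 1.65 | 1.45 |
| 2% / 6% | 1.65 | 1.79 |

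With equal early death of 2%, 5%, 10% and 15% and a PP odds ratio of 1.80, the all-dosed values are 1.76, 1.71, 1.62 and 1.55.

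**Hand check of the 8% / 2% row.**
- Deaths: 0.92 × 0.10 + 0.08 = 17.2% against 0.98 × 0.10 + 0.02 = 11.8%. The odds ratio for being alive is (0.828/0.172)/(0.882/0.118) = 0.64.
- mRS 0 to 2 (54% in PP): 0.92 × 0.54 = 49.7% against 0.98 × 0.54 = 52.9%, odds ratio 0.88.
- The fitted common value of 0.85 lies between these. In PP both odds ratios are 1.00.

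With 60 patients per arm, 8% and 2% are about 5 patients and 1 patient (60 × 0.08 = 4.8; 60 × 0.02 = 1.2), so a handful of patients is enough.

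**The case against.** The best defence is that the plan covers the endpoints that matter most. The ITT analyses of TCD, mRS and GOSE are unconditional, so early deaths are scored 6 and 1 there. Early harm would also show elsewhere: Section 7 gives deaths by arm with a Kaplan-Meier plot, adverse events leading to discontinuation, the size of each population, and withdrawal reasons and timing. The trial is Phase II with exploratory efficacy, the MCA-velocity and mRS objectives in Section 2 refer to a minimum of 7 days of treatment, and Sections 4.1 and 6.9 disclose the choice. All of this stands, and it makes PP a reasonable lead set for TCD. It does not help the eight endpoints without a guaranteed ITT analysis, and it leaves PP as the lead result for the key secondary endpoints.

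A reader might infer more than the document supports:
- *That the death scores never reach early deaths.* This is true of PP only; they do in the ITT analyses of mRS and GOSE.
- *That deterioration as such excludes a patient.* Dosing can continue by nasogastric tube. A patient is lost only if fewer than ten doses are given.
- *That the effect is biased.* With equal early loss and no effect, the odds ratio is 1.00 in both sets. Direction otherwise depends on rates not given.
- *That a Day 7 mRS of 6 is almost impossible in PP.* A first dose at 48 h puts dose 10 at 156 h (Day 6.5), but a first dose at 12 h puts it at 120 h (Day 5).
- *That the TCD result is materially shifted.* This needs an assumed exclusion split and an assumed correlation between exclusion and outcome. For 24% against 14% excluded, the shift is 0.075 to 0.105 SD at correlation 0.5 to 0.7, but only 0.015 to 0.045 SD at 0.1 to 0.3. The SAP supplies neither input.

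**Conclusion.** The structural point holds. The primary efficacy set excludes anyone who dies or permanently stops before about 4.5 days after the first dose, and within that set the SAP's death rules cannot act on those patients. The PP effect on clinical outcome can be biased either way if early loss differs by arm, and a real benefit is somewhat overstated if early loss is equal: 1.67 against 1.58 at 6% per arm, about 12% on the log scale (ln 1.67 / ln 1.58 = 0.513/0.457).

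The actual size cannot be stated. All the illustrative odds ratios rest on an assumed mRS distribution and assumed early-death rates of 2% to 15% per arm. Planned ITT analyses limit the consequence for mRS and GOSE. It is greatest for SF-36, CLCE-24, BICRO-39, SAHOT, length of stay, DCI, infarct and Triple H. For the last three the issue is that patients lost early, and any events they had, leave the comparison, since no death score applies.

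**What to change.** In Sections 4.1 and 6.2, make the existing ITT (all-dosed) set primary for the clinical outcomes: mRS, GOSE, SF-36, CLCE-24, BICRO-39, SAHOT, length of stay, DCI, infarct and Triple H. At the least, analyse all of them in that set unconditionally by deleting the discrepancy condition in Section 6.2, and align the summaries in Section 7. Keep the 10-dose PP set as the on-treatment analysis; it may stay primary for TCD. Tabulate PP exclusions by arm and reason, with death as its own category. Use one clock for the 7-day rule in Sections 4.1 and 6.9.

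The cost is SAP wording and a few more analyses. The analyses need no new data and no new population. Outcomes will be somewhat diluted by briefly treated patients. The change does not alter the rule that ITT patients are analysed by treatment received, so this set is still not a full intention-to-treat comparison, and the report should say so.

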## 5 Primary and Secondary Variables

### 5.1 Trans-Cranial Doppler

An initial TCD reading is taken within 48 hours of ictus. Subsequent TCD readings are then taken three times a week on alternate days (according to standard care procedures). They are performed at least until Day 7 post ictus ( $\pm 1$ ) and then until no longer clinically indicated. Table 1 describes the data collected at each timepoint noting that the individual value recorded represents the maximum of the mean flow recorded during the recording period.

**Table 1. TCD Recordings**

| Reading                                           | Units/Response |
|---------------------------------------------------|----------------|
| Left Middle Cerebral Artery Mean Flow Velocity    | cm/s           |
| Right Middle Cerebral Artery Mean Flow Velocity   | cm/s           |
| Left Internal Cerebral Artery Mean Flow Velocity  | cm/s           |
| Right Internal Cerebral Artery Mean Flow Velocity | cm/s           |
| Assessment Performed                              | Pre/Post       |
| Lindergaard Ratio Left                            | none           |
| Lindergaard Ratio Right                           | none           |

The primary endpoint is defined as the maximum of all left middle cerebral artery mean flow velocities (MCA-MFV) and right MCA-MFV values recorded after the first dose of randomised therapy including any taken after Day 7.

Baseline values will be defined as:

- The lowest of the left and right MCA-MFV values recorded at the earliest TCD assessment made within 2 days of first dose
- If a patient does not have a TCD recorded within 2 days of dosing, a predicted baseline value will be imputed based on their age, WFNS score (1 to 5), a past medical history of hypertension (yes/no), surgical procedure (clipping, coiling, none), log-CRP and centre as described below.

Amongst patients with baseline values recorded within 2 days of dosing, their baseline value will be regressed on age, WFNS score, hypertension, surgical procedure, log-CRP and centre. The imputed value for patients with a missing baseline value will equal  $\mu + \sum x_{ij}\beta_j$  where  $x_{ij}$  represent the observed values of the  $j$  covariate levels for the  $i^{\text{th}}$  patient and  $\beta_j$  the corresponding parameter estimates from the regression amongst patients with observed baseline values.

Supplementary analyses will also be performed on the mean of the three largest right or left MCA-MFV recorded at any timepoint after dosing. Additionally, an analysis will be performed to describe the effect over time with timepoints grouped, relative to date of Ictus, as Days 3-4, 5-6, 7-9, 10-14, 15-21, 22-28. Within each timepoint the largest MCA-MFV value will be included in the analysis for each patient. For these two analyses, the same baseline as the primary analysis will be used. Using the timepoint analysis the mean effect of Days 5 to 9 will also be estimated.

The analysis of Lindergaard ratio will mirror the primary analysis of MCA-MFV values: the maximum of all ratios recorded after the first dose of randomised therapy will be analysed and

baseline will be defined as the lowest of the left and right ratios recorded at the earliest TCD recording made within 2 days of first dose, imputing data using the same model approach if baseline values are otherwise missing.

All TCD endpoints will be loge-transformed prior to analysis.

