**Table 11. Formal statistical analyses to be conducted and pre-planned supplementary and sensitivity analyses**

| Endpoint                     | Notes                                                                                                                                                                                                                                                                                                                                                                                                                                                                                                                                                   |
|------------------------------|---------------------------------------------------------------------------------------------------------------------------------------------------------------------------------------------------------------------------------------------------------------------------------------------------------------------------------------------------------------------------------------------------------------------------------------------------------------------------------------------------------------------------------------------------------|
| TCD                   | 
Primary: maximum post-dose MCA mean flow velocity
 
Sensitivity analysis:
 
 
Removing baseline data from the analysis model if it appears SFX-01 has had an effect by Day2
 
 
Supplementary analyses:
 
 
Mean of 3 largest post-dose MCA mean flow velocities
 
Maximum post-dose Lindergaard ratio
 
Maximum MCA mean flow velocity per timepoint
 
Mean effect over days 5 to 9 of maximum MCA mean flow velocity.
 
 |
| Modified Rankin Scale | 
Analysis at Day 7, 28, 90 and 180 and at discharge
 
Sensitivity analysis:
 
 
If more than 15% of patients have missing data at Day 180 in either treatment arm, the analysis at each timepoint will be repeated by carrying forward the
 
                                                                                                                                                                                                                                                     |

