## **6.8 Subgroup analyses**

Subgroup analyses will be performed for maximum post-dose MCA mean flow velocity, mRS at 90 days and GOSE at 90 days for the following variables: centre, WFNS score (1-3 v 4-5), Fisher grade, time from ictus (<24h, 24-48h, >48h), Age group ( $\leq 49$ , 50-59,  $\geq 60$ ), gender, surgical procedure (coiling, clipping, not done), location of aneurysm (anterior, posterior), main vessel of aneurysm (anterior, middle, internal, vertebrobasilar) and whether the patient developed a secondary bleed prior to randomisation. Additionally, a subgroup analysis of the primary TCD endpoint will be performed by baseline value split according to quartiles. Results will not be presented for any subgroup level that contains fewer than 10 patients.

Data will be analysed separately for each level of the subgroup. For the primary TCD endpoint, the ANOVA model will be re-run and the treatment effect and associated 95% confidence intervals presented. For mRS and GOSE at 90 days, the logistic regression model will be performed within each level of the subgroup with the odds ratio and associated 95% confidence intervals presented. Results from all subgroups will be presented in a forest plot for each endpoint separately.

If there is evidence of heterogeneity of the treatment effect amongst subgroups the following tests will be performed:

1. A treatment-by-subgroup interaction term will be added to a model containing the terms included in the primary analysis model together with the main effect of the subgroup if not already included in the model. The p-value for the change in model fit by adding the interaction term will be presented
2. A test of the collective heterogeneity amongst subgroups will be performed. This will be achieved by comparing a base model including treatment and all main effects of subgroups with a model containing all two-way interactions of treatment and subgroup. The p-value for the change in model fit by adding all of the interaction terms simultaneously will be presented and described as a global interaction test.

Age will be fitted as a continuous covariate in the interaction tests.

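### The per-timepoint TCD analysis does not exclude readings taken before the first dose, so a pre-dose velocity on Day 3 or 4 is an eligible Days 3-4 outcome

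*SAP*

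**What the plan says.** SAP 5.1 describes a supplementary analysis of effect over time, "with timepoints grouped, relative to date of Ictus, as Days 3-4, 5-6, 7-9, 10-14, 15-21, 22-28". The value taken from each window is set by one sentence: "Within each timepoint the largest MCA-MFV value will be included in the analysis for each patient". The sentence after it only says that the baseline is the same as in the primary analysis. Table 11 lists the analysis as "Maximum MCA mean flow velocity per timepoint". Section 6.4 gives the MMRM and its SAS code and adds no condition on when a reading was taken relative to dosing.

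The other TCD analyses do carry that condition:

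- The primary endpoint is the maximum of the left and right "values recorded after the first dose of randomised therapy including any taken after Day 7".
- The first supplementary analysis uses "the mean of the three largest right or left MCA-MFV recorded at any timepoint after dosing", listed in Table 11 as "Mean of 3 largest post-dose MCA mean flow velocities".
- For the Lindergaard ratio, "the maximum of all ratios recorded after the first dose of randomised therapy will be analysed".

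Four other statements bear on the point:

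- The first TCD is due within 48 hours of ictus, with later ones on alternate days, three times a week (5.1).
- Baseline is the lower of the left and right values at the earliest TCD within 2 days of first dose (5.1).
- Section 7 will split baseline values by whether they preceded dosing or fell on Day 1 or Day 2, so some pre-dose readings are expected.
- Section 6.8 plans a subgroup by "time from ictus (<24h, 24-48h, >48h".

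**The concern.** A velocity measured before any study drug cannot carry a treatment effect. If such a reading enters the MMRM as a Days 3-4 outcome, that patient adds no information on the drug to that window, and the estimated SFX-01:placebo ratio moves towards 1. Days 3-4 is the first point on the planned graph of treatment effects over time, so the early part of the curve is where this would show.

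There is a second, smaller problem. Baseline may itself be a pre-dose assessment. If that assessment falls on Day 3 or 4, its lower side becomes the baseline and its higher side can become the outcome. The model would then relate one side to the other at a single examination rather than a later reading to an earlier one.

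**Working it through.** The SAP states no figure on this point, so there is none to reproduce. The check compares wording and then asks when a pre-dose reading can fall in the first window.

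**Step 1: the post-dose condition, analysis by analysis**

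| Analysis | Condition in 5.1 | Post-dose in Table 11 | Time origin |
|---|---|---|---|
| Maximum MCA velocity (primary) | after first dose | yes | first dose |
| Mean of three largest | after dosing | yes | first dose |
| Maximum Lindergaard ratio | after first dose | yes | first dose |
| Maximum per timepoint | none | no | ictus |

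The text and code in 6.4 do not supply the missing condition.

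**Step 2: hours since ictus covered by Days 3-4**

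The SAP does not say whether the ictus date is Day 0 or Day 1 for these windows. The only day-count formula it shows, for length of stay in 5.11, adds 1, which makes the ictus date Day 1.

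- Ictus date = Day 1. Day 3 begins 48 h after the midnight that opens the ictus date. An ictus just before the next midnight is then 48 - 24 = 24 h old. Day 4 ends 96 h after the opening midnight. The range is about 24 to 96 h after ictus.
- Ictus date = Day 0. Everything moves one day later: about 48 to 120 h.

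**Step 3: how often a reading at t hours falls in the window**

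Assume that ictus clock times are spread evenly over the day (an assumption; the SAP gives no distribution).

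- Day 1 count, t from 24 to 48 h: share = (t - 24)/24. At 36 h this is 12/24 = 50%; at 42 h, 18/24 = 75%; at 47.9 h, 23.9/24 = 99.6%.
- Day 0 count, t from 48 to 72 h: share = (t - 48)/24. At 47.9 h it is 0; at 54 h, 6/24 = 25%; at 60 h, 12/24 = 50%.

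On the Day 1 count, a first TCD made on schedule within 48 h can already lie in the window. If the first dose follows it, still within 48 h of ictus, that pre-dose reading is an eligible outcome. On the Day 0 count, this requires a first dose later than about 48 h after ictus.

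**Step 4: whether an eligible reading becomes the outcome**

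It does so if it is the largest in the window. With TCDs on alternate days, a two-day window will usually hold one assessment, so a pre-dose assessment there will often be the only candidate.

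**Step 5: direction**

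If a share f of patients have a pre-dose value as their Days 3-4 outcome, similar in both arms, the expected log-ratio in that window is roughly multiplied by (1 - f). The SAP gives neither f nor an expected effect at Days 3-4, so only the direction can be stated.

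**The case against.** The case that this hardly matters is strong in several respects.

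- **The windows already remove most pre-dose readings.** Patients present within 48 hours of ictus, the first TCD is due in the same period, and the first window opens at Day 3. Section 6.4 adds that many baselines were recorded shortly after dosing. This stands, and it is why the number affected is probably small.
- **Early post-dose readings may also show little.** Section 6.4 expects no treatment effect shortly after dosing. In a patient first dosed on Day 3, a post-dose reading on Day 3 or 4 might carry little effect too. Much of any attenuation in that window therefore comes from counting days from ictus, which is a deliberate choice. This stands, and it limits what the fix recovers.
- **Some affected patients may leave the PP population.** Section 6.9 describes PP as at least 10 doses within 7 days of ictus. With ictus on Day 1 and a single dose late on Day 3, twice-daily dosing gives 1 + 2 × 4 = 9 doses by the end of Day 7. This stands only in part: 4.1 counts the 7 days from the first dose, and TCD endpoints are also analysed in the ITT population.
- **The purpose implies post-dose readings.** A description of effect over time suggests that intent. But the neighbouring analyses state the condition and this one does not, so a programmer following the text would include pre-dose values.

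A reader might infer from the over-48-hour subgroup level that the plan expects late-dosed patients. Section 6.8 does not say at which event that interval ends or that anyone falls in the level. It may be a catch-all, and levels with fewer than 10 patients are not presented.

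**Conclusion.** The gap is real but minor. The selection rule for the per-timepoint analysis does not exclude pre-dose readings, alone among the TCD velocity and ratio maxima. Any that fall on Day 3 or 4 are eligible outcomes and pull the Days 3-4 ratio towards 1.

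The effect is confined to one of six windows in a supplementary analysis. A pre-dose reading in Days 5-6 would need a first dose on Day 5 or later, so later windows and the Days 5-9 mean are essentially unaffected. The primary endpoint is expressly post-dose and is not affected.

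No percentage dilution can be given, because the SAP states neither the share of patients affected nor an expected early effect. A reader might also conclude that pre-dose readings will in fact be counted as outcomes. The text supports only that it does not exclude them; whether any occur depends on dosing times, TCD times and the unstated day count.

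**What to change.** Make three wording changes to the SAP:

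1. In 5.1, Table 11 and 6.4, define the per-timepoint value as the largest MCA-MFV value recorded after the first dose of randomised therapy within each timepoint.
2. State that a window containing only pre-dose readings is treated as missing for that patient in the MMRM, which accommodates missing visits.
3. State whether the ictus date is Day 0 or Day 1 for the TCD windows.

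No new data are needed: the primary endpoint already requires each reading to be placed before or after the first dose. Table 1 also has a Pre/Post field, but its reference event is not stated and should be confirmed before it is used for this. The cost is slightly fewer observations, and so slightly less precision, in the Days 3-4 window.
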